**Methods:**

The trial will enrol 20 patients in total. After completion of the screening procedures, participants will receive the first dose of dostarlimab within 28 days. Dostarlimab will be administered at the dose of 500 mg evry 3 weeks for the first 5 cycles, and at 1000 mg every 6 weeks thereafter. Treatment will continue until disease progression, unacceptable toxicity, or completion of 1 year of treatment. The first 6 patients will be enrolled in a safety-lead-in phase, if no dose-limiting toxicities (DLTs) will occur within the 21 days in the first 6 participants, trial will continue. Patients will be monitored for the emergence of adverse events until 90 days after the last dose of treatment. Tumour response will be assessed as objective response rate (ORR) at cycle 4, cycle 8 and end of treatment. Tissue, bloods, and stool samples will be collected at baseline, on treatment and at end of treatment to satisfy the related translation plan.

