## Methods

### Trial design

The StarKap study is a single centre open label phase Ib trial assessing the safety, tolerability and preliminary efficacy of dostarlimab in patients affected by cART-refractory KS. The trial is sponsored by Imperial College London and is currently open to recruitment at Chelsea & Westminster Hospital, in London, UK.

A phase Ib, single-arm, open label study describing safety and tolerability of dostarlimab is necessary to answer the question of feasibility of anti-PD-1 immunotherapy in PLWH and KS. No dose-escalation was deemed necessary in this population due to the non-linear relationship between exposure and immune-mediated toxicity and the lack for dose-limiting toxicities observed in dose escalation studies of dostarlimab [15, 16].

The study will enrol 20 adult patients aged (aged ≥ 16 years) affected by HIV-related KS, fulfilling the criteria of cART-refractory KS. To this end, patients will be required to have KS that progressed or remained stable after at least 3 continous months of cART, with HIV-RNA < 200 copies/ml and CD4 count of at least 100 cell/µL at screening. Upon completion of screening procedures and confirmation of eligibility, patients will start treatment with dostarlimab within 28 days from screening. Dostarlimab will be administered intra-venously according to summary of product characteristics, at the dose of 500 mg every 3 weeks for the first 4 cycles and at 1000 mg every 6 weeks for the following cycles. Dostarlimab will be continued until completion of 1 year, loss of clinical benefit, inacceptable toxicities or withdrawal of consent, whichever comes first.

A safety lead-in phase will initially require a total of 6 patients, who will be observed for the emergence of dose-limiting-toxicities (DLTs) over a 21-days window from dosing. Following discussion within the trial steering committee it was opted to maintain a standard 21-days safety window for the first 6 subjects with a particular focus on the assessment of events of immune-reconstitution as well as qualitative and quantitative changes in parameters reflective of HIV control. The decision to enrol 6 subjects for the initial safety lead-in phase is in line with standard clinical trial design practice for early-phase trials. This number is generally considered sufficient to detect any early DLTs [17].

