Once all the 6 patients have completed the 21-day safety window observation, trial steering committee (TSC) will review the AE profile and, in the absence of DLTs advise on continuation of recruitment to the subsequent expansion phase leading to enrolment of 20 patients in total. If ≥ 1 DLTs will occur within the first 21 days in the patients enrolled in the safety-lead-in phase, the trial will be prematurely interrupted. During the TSC review, the enrolment of new patients will be paused. In the absence of AEs preventing to do so, the treatment of the first 6 patients will continue as planned, without waiting for the TSC review. The definition of DLTs is reported in Table 1. No dose-reductions are allowed. In general, dostarlimab must be withheld for drug-related toxicities of grade 3, but may be resumed upon recovery to Grade ≤ 1; dostarlimab will be permanently discontinued for any drug-related AE of grade 4. Treatment delays for up to 21 days are permitted in the case of AEs. Any AEs requiring a treatment interruption > 21 days will prompt treatment interruption.

**Table 1 Tab1:** Definition of dose limiting toxicities according to CTCAE v.5

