**Secondary**	
A) To characterize the efficacy of dostarlimab in cART-refractory HIV associated Kaposi Sarcoma	1. Objective Response rate (ORR) evaluated at week 10 and week 31 (± 7 days) and end of treatment by modified AIDS Clinical Trial Group (ACTG) Kaposi sarcoma (KS) response criteria. For patients with visceral involvement Response Evaluation Criteria In Solid Tumours (RECIST) v1.1 will be used to complement modified ACTG response criteria 2. Progression free survival (PFS) from screening 3. Time to progression from the first evidence of documented objective response to dostarlimab

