
### Statistical analysis

With safety being elected as primary clinical endpoint for the study, no power calculation for hypothesis testing was required to formally power the study. Justification for a sample size of 20 subject was based on previous experience in the use of pembrolizumab in HIV-associated cancers [9, 22].

An interim analysis on adverse events will be conducted after the 6 th subject clears the 21-days safety window. Pending review of safety data by the trial steering committee in the first 6 subjects, in the absence of significant toxicity, the study will continue to the recruitment of the remaining 14 subjects without pause.

The final efficacy analysis on the whole will be conducted at the end of the study after the last patient has completed the treatment.

The safety population will include all subjects receiving at least one dose of dostarlimab. All participants who receive at least one dose of dostarlimab and undergo efficacy evaluation will be included in the efficacy population. No patients will be replaced as this would introduce bias; drop-out is likely to be informative in this population.

The primary outcome will be presented using descriptive measures of safety such as frequencies and percentages of adverse events grouped as categorical variables and means and standard deviations for normally distributed continuous variables.

Efficacy endpoints will be estimated descriptively by documenting ORR and progression free survival rates (PFSR) at 12-weekly timepoints. Progression free survival will be estimated using the Kaplan–Meier method from screening to progression or death. The PFSR estimates the proportion of participants who do not progress and are alive at 12 weeks timepoint.

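### ORR and PFS rates are to be read every 12 weeks from screening, but the stated tumour assessments are at week 10, week 31 and end of treatment, so some rates would mostly repeat an earlier status and read too high

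*Protocol article*

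**What the plan says.** All references are to the protocol article.

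- **Reading times.** Statistical analysis plans "documenting ORR and progression free survival rates (PFSR) at 12-weekly timepoints". It then defines the rate for a single time: "The PFSR estimates the proportion of participants who do not progress and are alive at 12 weeks timepoint".
- **Estimator and time origin.** "Progression free survival will be estimated using the Kaplan–Meier method from screening to progression or death".
- **Assessment times.** Table 3, secondary endpoints: "Objective Response rate (ORR) evaluated at week 10 and week 31 (± 7 days) and end of treatment". The abstract (Methods) gives the same occasions as cycles: "Tumour response will be assessed as objective response rate (ORR) at cycle 4, cycle 8 and end of treatment".
- **Screening to first dose.** Trial design: "patients will start treatment with dostarlimab within 28 days from screening".
- **Treatment length.** Up to 1 year, and shorter with progression, loss of clinical benefit, toxicity or withdrawal (abstract and Trial design).

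The article states no other tumour assessment, no expected PFS and no method for interval-censored progression times.

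**The concern.** The reading grid and the assessment schedule do not fit each other. Kaplan–Meier with progression dated at detection moves only when someone looks. A rate read many weeks after the last look therefore reports the status at that look, minus any deaths and any progression found off schedule. The resulting error always runs upward.

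The time origin adds to this. The PFS clock starts at screening, while the assessment weeks match the dosing calendar, which starts at first dose. The 12-week rate, the only one the article defines explicitly, can therefore fall before a patient's first on-treatment assessment.

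As worded, the 12-weekly grid also covers ORR, which Table 3 places at week 10, week 31 and end of treatment.

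The trial has a single arm, so readers will judge its PFS rates against other studies. Up to four reported rates would look like four pieces of information when about two scheduled looks stand behind them, and an artefact of the calendar could be taken for drug activity.

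**Working it through.** **1. Reproduce the assessment weeks.** Count first dose as day 0, the start of week 1. With four 3-weekly cycles, the first 6-weekly cycle 3 weeks after cycle 4, and 6-weekly dosing after that (one reading of Trial design):

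- cycle 4: 3 × 21 = day 63, the start of week 10;
- cycle 5: 4 × 21 = day 84;
- cycle 8: 84 + 3 × 42 = day 210, the start of week 31.

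Table 3's weeks are reproduced, so they run from first dose and agree with the abstract's cycles. The abstract has five 3-weekly cycles where Trial design has four. Depending on the interval before the first 6-weekly dose, cycle 8 falls in week 28, 31 or 34. Those two passages need reconciling, but the result below uses Table 3's weeks as stated.

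**2. Compare the grid with the schedule.** From first dose, the windows cover weeks 9–11 and 30–32. None contains 12, 24, 36 or 48. From screening, each assessment moves later by the screening-to-dose gap (0 to 4 weeks). Weeks elapsed since the last scheduled assessment, taking the week labels 10 and 31 as elapsed weeks:

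| Reading | Gap 0 wk | Gap 2 wk | Gap 4 wk |
|---|---|---|---|
| Week 12 | 2 | 0 | none yet |
| Week 24 | 14 | 12 | 10 |
| Week 36 | 5 | 3 | 1 |
| Week 48 | 17 | 15 | 13 |

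**3. When the first assessment misses the 12-week reading.** Twelve weeks is 84 days. Nominally, 63 + 21 = 84, so a gap over 21 days puts the first assessment after the reading. At the late edge of the window, 70 + 14 = 84, so a gap over 14 days does. Both lie within the 28 days allowed.

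**4. Size of the bias.** The article gives no PFS assumption, so these medians are assumptions. With exponential PFS, S(t) = exp(−ln 2 × t / median). If progression is found only at scheduled assessments, the value read at t is S(last assessment at or before t), and bias = S(last) − S(t). With no screening gap (6 months = 26.09 weeks):

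| Median | Week 24: true → read | Week 48: true → read |
|---|---|---|
| 6 months | 52.9% → 76.7% (+24) | 27.9% → 43.9% (+16) |
| 12 months | 72.7% → 87.6% (+15) | 52.9% → 66.2% (+13) |
| 24 months | 85.3% → 93.6% (+8) | 72.7% → 81.4% (+9) |

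A simulation of 20,000 trials of 20 patients gave the same values. Across gaps of 0 to 4 weeks and medians of 6 to 24 months:

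- week 24: +6 to +24 points;
- week 48: +7 to +16 points;
- week 36: +0.5 to +5.5 points;
- week 12: 0 to +4 points with gaps up to 2 weeks, but +8 to +27 if every patient had a 4-week gap.

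If half of the between-visit progressions are found off schedule, each figure halves.

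**5. Sensitivity to the week count.** Taking the assessments at day 63 and day 210 (9 and 30 elapsed weeks) lengthens the week-24, -36 and -48 gaps by one week. At a 6-month median with no screening gap, week 24 becomes S(9) − S(24) = 78.7% − 52.9% = +26 points, and week 48 becomes S(30) − S(48) = 45.1% − 27.9% = +17. The conclusion does not change.

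**6. Scale.** With n = 20 and a rate of 50%, the standard error is √(0.25/20) = 11 points. At the shorter medians the bias exceeds this, and a confidence interval would not show it.

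**The case against.** Much of the opposing case stands.

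- **The schedule quoted is for ORR.** The article does not say that progression is sought only then. End of treatment is an assessment in its own right, and progression or loss of clinical benefit brings it forward. Dosing visits every 3 or 6 weeks are further chances to see skin progression. The trial flowchart is not visible here. All of this shrinks the bias, and it is why the figures above are for scheduled detection only. It cannot reverse the direction.
- **Weeks 24, 36 and 48 are inferred.** Only 12 weeks is named. On the narrowest reading, a single 12-week rate, what remains is the time-origin problem in step 3.
- **The size rests on assumed medians.** Hence a range rather than one figure.
- **PFS is descriptive and secondary.** There is no comparator, test or decision rule.

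A reader might infer two stronger claims that the article does not support.

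- *That every reading falls just before the next assessment.* Week 36 follows the week-31 assessment closely, week 12 usually follows the week-10 one, and week 24 lies some 6 to 10 weeks before the next.
- *That patients with toxicity are assessed later and so seem to progress later*, because "Treatment delays for up to 21 days are permitted in the case of AEs". Table 3 fixes calendar weeks, "evaluated at week 10 and week 31 (± 7 days) and end of treatment", and the cycles in the abstract reproduce those weeks. Nothing says that a delayed cycle overrides Table 3.

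**Conclusion.** The point holds in limited form. As written, the 12-weekly reading times do not line up with the stated tumour assessments, and the screening-based clock can put the 12-week rate ahead of a patient's first on-treatment assessment.

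If the grid extends past week 12, the week-24 and week-48 rates are the ones materially affected, and week 36 hardly is. The ranges in step 4 rest on four assumptions: exponential PFS, medians of 6 to 24 months, the same screening gap for all patients, and no off-schedule detection. They are therefore nearer a ceiling than an expected value.

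The weakness lies in how a descriptive secondary endpoint is reported. It does not touch the primary safety objective or any rule for continuing the trial. It is worth correcting because the bias runs one way and the correction is cheap.

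**What to change.** 1. Count PFS from first dose instead of screening.
2. Replace the 12-weekly grid with the scheduled assessments. Report ORR at those assessments, and read PFS rates at the close of the windows: week 11 (63 + 7 = day 70) and week 32 (210 + 7 = day 217). Read the last rate after the 1-year end-of-treatment assessment, and give that assessment a stated window. Without one, a late assessment would again leave a patient carried forward from about week 31.
3. Add a sensitivity analysis that treats progression as interval-censored between the last progression-free assessment and the one that found it.

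For an assessment held on its nominal day, reading at window close leaves one week of drift. At a 6-month median that is S(9) − S(10) = 78.7% − 76.7%, about 2 points at week 11, and S(30) − S(31) = 45.1% − 43.9%, about 1 point at week 32.

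The cost is protocol or analysis-plan wording and a short extra analysis, with no added visits or scans. The one downside is that the reading times are not round multiples of 12 weeks, so side-by-side comparison with studies that report 12- or 24-week rates is less direct.

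### PFS is timed from screening but analysed only in patients later dosed and evaluated, which credits up to 28 pre-treatment days and can inflate the 12-week rate

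*Protocol article*

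**What the plan says.** The protocol article fixes the PFS origin twice, the same way. Table 3 lists "Progression free survival (PFS) from screening" among the secondary endpoints, and the Statistical analysis section applies the Kaplan–Meier "method from screening to progression or death". Landmark results are to be reported as "progression free survival rates (PFSR) at 12-weekly timepoints".

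The analysis set is also fixed, in the Statistical analysis section: "All participants who receive at least one dose of dostarlimab and undergo efficacy evaluation will be included in the efficacy population". The article does not name this set again beside PFS, but Table 3 places PFS under the efficacy objective, so this is the natural reading.

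The interval between origin and treatment is bounded under Trial design: "patients will start treatment with dostarlimab within 28 days from screening". The Abstract puts it as "After completion of the screening procedures, participants will receive the first dose of dostarlimab within 28 days".

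Response is "evaluated at week 10 and week 31 (± 7 days) and end of treatment" in Table 3. The Abstract ties the same assessments to treatment: "Tumour response will be assessed as objective response rate (ORR) at cycle 4, cycle 8 and end of treatment".

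Nothing in the article corrects PFS for the interval before first dose or adds a PFS analysis from first dose.

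**The concern.** The clock starts before the event that admits a patient to the analysis. Someone who dies between screening and first dose, or worsens and is not treated, never enters the efficacy population. Everyone who is treated keeps that interval as progression-free time. This is immortal-time bias, and it pushes PFS upward.

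A screening origin would be coherent if everyone enrolled at screening were analysed. Combined with a treated-only set, it is not. The requirement for an efficacy evaluation acts in the same direction: a patient who dies after dosing but before any assessment also drops out, so the selection can extend beyond first dose.

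Table 3 presents PFS as a measure of dostarlimab's efficacy. In a single-arm trial of 20 patients there is no concurrent arm carrying the same shift, so it goes straight into the reported estimate. A 12-week rate from screening can reflect as little as 12 − 4 = 8 weeks after first dose.

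**Working it through.** The article states no PFS median or rate, so there is no figure of its own to reproduce. The question is how far the origin moves the estimates.

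**Inputs from the article.** Gap g from screening to first dose: 0 to 28 days (Trial design). Landmarks: 12-weekly (Statistical analysis). Response visits: week 10, week 31 (± 7 days) and end of treatment (Table 3). **Assumptions.** Exponential PFS from first dose, with the medians shown below; 1 month = 30.4375 days.

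**1. Event times and median.** Time from screening = time from first dose + g. Each event time lengthens by that patient's g. With a common gap the median lengthens by exactly g; otherwise by at most 28 days, which is 28/30.4375 = 0.92 month.

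**2. The 12-week rate, progression dated continuously.** If S is the survival function from first dose, the rate reported from screening is S(12 − g), with S(t) = 0.5^(t/median) and g in weeks.

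| Assumed median | From first dose, S(12) | 2-week gap, S(10) | 4-week gap for all, S(8) |
|---|---|---|---|
| 12 weeks | 50.0% | 56.1% | 63.0% |
| 26 weeks | 72.6% | 76.6% | 80.8% |
| 12 months (52.2 weeks) | 85.3% | 87.6% | 89.9% |
| 18 months (78.3 weeks) | 89.9% | 91.5% | 93.2% |

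The last column is a ceiling. A simulation with n = 20, gaps uniform on 0–28 days and a 6-month median gave 72.3% from first dose and 76.5% from screening. The effect shrinks at later landmarks: for a 6-month median at the full gap, it is 58.8 − 52.9 = 5.9 points at 24 weeks, 42.7 − 38.4 = 4.3 at 36 and 31.1 − 27.9 = 3.2 at 48.

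**3. Progression dated only at scheduled visits.** The cycle 4 visit falls 63 days after first dose.

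- Week 12 is day 84. An on-time visit passes it only if g > 84 − 63 = 21 days; a visit 7 days late, only if g > 84 − 70 = 14 days. With a 2-week gap and an on-time visit, the progression is dated at 63 + 14 = 77 days and still counts as an event by week 12.
- The latest possible date for that visit is 70 + 28 = 98 days, before week 24 (day 168).
- The cycle 8 visit is 210 ± 7 days after first dose, so 203 to 217 + 28 = 245 days from screening. That lies between week 24 (168) and week 36 (252) whatever the gap.
- An end-of-treatment visit at about one year is already beyond week 48 (336).

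So only the 12-week rate can move. In simulation with visit dating and the same gaps, it went from 78.3% to 83.8% for a 6-month median and from 88.7% to 91.6% for a 12-month median. The 24-, 36- and 48-week rates were identical under the two origins.

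**4. Which clock the response visits follow.** Use the Trial design schedule (3-weekly for four cycles, then 6-weekly), taking cycle 5 three weeks after cycle 4, and count first dose as day 1. Cycles 1 to 8 then fall on days 1, 22, 43, 64, 85, 127, 169 and 211. Day 64 is in week 10 and day 211 in week 31, matching Table 3. ORR is therefore read on a first-dose clock while PFS runs from screening. The Abstract gives five 3-weekly cycles instead of four, which would put cycle 8 on day 190 (week 28). The two schedules need reconciling, but week 10 is the same under both.

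**The case against.** Several points on the other side are fair.

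- **Only survival is guaranteed in the gap.** Nothing in the eligibility criteria bars dosing a patient whose disease worsens after screening, and progression on cART is itself a route to eligibility. A reader might call the interval guaranteed event-free. The article supports only the narrower statement that death is excluded by selection and no response assessment is scheduled there.
- **Not every PFS estimate is shown to be overstated.** With visit-dated progression the later landmark rates do not change. Deaths, and progressions found between visits, would still shift.
- **28 days is a ceiling, and actual gaps are unknown.** The article does not say which date counts as screening. Trial design also speaks of completed screening procedures, so the Abstract's wording is weak evidence that a longer gap is allowed.
- **There may be a partial offset.** If baseline lesions are measured at screening, growth before first dose counts against dostarlimab at week 10. The article does not give enough detail to size this.
- **The stakes are limited.** PFS is a descriptive secondary endpoint with no hypothesis test. At a rate of 72.6% with n = 20, the binomial standard error is √(0.726 × 0.274 / 20) ≈ 10 points, larger than the 4 to 8 points in the 26-week example.

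These points limit the size and reach of the problem but do not remove it. Sampling error does not excuse an avoidable bias, and stating the origin openly does not let a reader undo it without each patient's gap.

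**Conclusion.** The concern holds in a limited form. The PFS origin precedes entry to the analysis set by up to 28 days, and nothing in the article corrects for it. Event times lengthen by each patient's gap and the median by at most 28 days. The 12-week rate is the estimate most exposed: about 4 points at a 2-week gap and at most about 8 at 4 weeks, given a 26-week median with exponential, continuously dated PFS. A shorter true median gives a larger effect and a longer one a smaller effect. Under strict visit dating, the 12-week rate moves only for patients whose gap is long enough to carry the cycle 4 visit past day 84.

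A reader might also infer that the result will look better than any series counted from first dose. The article does not support that: such a comparison depends on drug effect and case mix, and no external PFS benchmark is planned.

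**What to change.** In Table 3 and the Statistical analysis section, define PFS and its landmark rates from the date of first dostarlimab dose to progression or death from any cause. Report the screening-origin version only as a sensitivity analysis. This puts PFS on the same clock as the response visits.

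Analyse PFS in all dosed patients. This is a separate change to the stated efficacy population. It is needed because the evaluation condition selects patients who survive to an assessment, and a new origin alone would leave that selection in place.

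Keeping the screening origin and analysing everyone enrolled from that point would also be consistent, but it would describe the strategy from enrolment rather than outcome on dostarlimab.

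Cost: no new visits or patients, and only the date of first dose is needed. Reported PFS becomes slightly shorter. Because the trial opened in May 2023 and is recruiting, redefining a secondary endpoint needs a documented amendment. The primary safety endpoint, ORR and sample size are unaffected.
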